**a. Specific Aims**

**Specific Aim 1: To estimate the effect of receiving CBCT on empathic accuracy and resilience among chaplain residents providing spiritual care to hospitalized patients.**

We will conduct a naturalistic study of up to 30 chaplain residents serving the Spiritual Health department of Emory Healthcare, and who will receive CBCT during the first unit of their year-long residency (the early-start group) or approximately midway through the residency year (the delayed-start group). Empathic accuracy and resilience will be measured for all participants before the early-start group receives CBCT (baseline, or T0); after the early-start group completes CBCT (T1); before the delayed-start group receives CBCT (T2), and after the delayed-start group completes CBCT (T3). See **Figure 3** for study schematic. The change in mean score of empathic accuracy and resilience measures from T0 to T1 among participants in the early-start group will be compared to the change in mean score among participants in the delayed-start group over the same time period.

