**2. Design**

1. **Sample:**

Emory Healthcare chaplain residents will be asked to view the empathic accuracy video scenarios and complete questionnaires at four time points during the residency year. Chaplains will be asked to wear ambulatory recording devices that record chaplain-patient interactions.

Emory Healthcare patients will be asked to complete self-report assessments before and after their Spiritual Health consult. Patients will be informed of chaplains use of ambulatory recording device for research purposes.

No children, prisoners or other vulnerable populations will be included in this study.

*Inclusion Criteria*: Chaplain residents with Spiritual Health at Emory Healthcare or patient of Emory Healthcare.

*Exclusion Criteria*: None

b. **Setting:**

Consenting chaplains will view the empathic accuracy videos and complete the study questionnaires at one or more of the Emory Healthcare campuses (EUH, EUHM, Saint Joseph’s, Emory Johns Creek, and Wesley Woods).

Consenting patients will complete self-report assesments and spiritual health consults at one or more of the Emory Healthcare campuses (EUH, EUHM, Saint Joseph’s, Emory Johns Creek, and Wesley Woods).

c. **Recruitment:**

Chaplain residents and Emory Healthcare patients will be approached in person at the Emory Healthcare campuses by a researcher and will provide written consent.

d. **Procedures**:

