During their training program, chaplain residents will provide spiritual consults to patients throughout the Emory hospital system. We will examine whether patient (n = 300) outcomes are improved for those receiving chaplain spiritual care augmented by CBCT, in comparison to those receiving spiritual care from chaplains who receive CBCT at the end of their residency program. To this end, study personnel will shadow chaplain residents in both groups and will administer self-report assessments of negative symptomology (depression, anxiety, and loneliness) and well-being (quality of life, hope) to consented patients. In addition, study personnel will audio record chaplain-patient interactions. Patient outcomes will be gathered from retrospective chart reviews and will include use of opioid pain medication, duration of stay, patient’s denial of care, and patients’ Press Ganey satisfaction scores.

In a final step, using patient chart reviews we will examine chaplain and patient factors that may mediate the link between spiritual consults and improved patient outcomes. Specifically, we will examine whether chaplain empathic accuracy or self-reported compassion mediate the impact of spiritual care consults on patient health outcomes. We will also examine whether patients’ well-being (hope, quality of life), or negative symptoms (depression, anxiety, loneliness) mediate the impact of spiritual care consults on patient health outcomes.

We will also use the ambulatory ambulatory audio recordings of the chaplain-patient interactions to interrogate which aspects of the chaplain-patient interaction mediate improved patient outcomes (see Figure 4). Spiritual consult audio recordings will be coded by 2 trained, independent CBCT instructors for CBCT content. They will also be coded for linguistic and behavioral elements derived from existing models of compassionate interaction in the hospital environment[^9^](#_ENREF_9).

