**Audio Recordings:**

Chaplain residents will wear a recording device that will record chaplain-patient interactions. Patients will be informed that they can stop the recording at any time and that they can ask for their recording to be deleted at any time if they no longer wish for it to be a part of the study. Audio recordings will be de-identified, such that patient and chaplain are only linked with participant IDs and identity will not be available to anyone coding the recordings. Patients and chaplain participants will complete an assent form to indicate how their recordings can be used, including whether recordings can be used for other research projects by our team, by other researchers, and for scientific presentation of these data.

1. **Data analysis**

We will analyze the data to test the hypothesis that CBCT improves chaplain residents’ empathic accuracy and resilience in a hospital setting. SAS 9.4 and SPSS 23 will be used to conduct statistical analysis of the collected data. Descriptive statistics will be used to describe selected characteristics of participants by group, expressed as frequencies and percentages. The primary outcomes of empathic accuracy, compassion fatigue, compassion satisfaction, empathy, anxiety, and depressive mood will be measured as pre-to-post differences in the measurement scores, i.e., T1 – T0. For the early-start group and T3 – T2 for the delayed-start group. We will examine the effect of CBCT by analyzing the correlated, repeated-measure data (T1 – T0) – (T3 – T2) using mixed linear models, implemented in SAS Proc Mixed. Mean pre-to-post differences will be compared across groups.

To evaluate whether the effects of CBCT persist over time, differences between mean scores on measures of empathic accuracy and resilience for the early-care group will be compared across four time points: from baseline measurement to early-group post-CBCT measurement (T1 – T0), from early-group post-CBCT measurement to delayed-group pre-CBCT measurement (T2 – T1)_,_ and from delayed-group pre-CBCT measurement to delayed-group post-CBCT measurement (T3 - T2). To evaluate whether the effects of CBCT depend on the timing of program delivery, the differences between mean scores on empathic accuracy and resilience will be compared for each group during the period following receipt of the CBCT program; that is, (T1 – T0) – (T3 – T2).

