To evaluate whether CBCT-informed interventions improve patient outcomes, descriptive statistics (means, standard deviation, standard error) will be used to characterize baseline demographics and responses to self-report assessments. All data will be evaluated for normality, and appropriate procedures will be performed in cases where normality is violated. To evaluate whether CBCT-informed spiritual consults impact patients’ negative symptoms, well-being, and patient health outcomes (duration of stay and patients’ Press Ganey satisfaction scores) we will conduct independent samples t-tests. Dichotomous variables (denial of treatment, opioid use) will be evaluated using chi square tests.

To explore chaplain and patient mediators of the impact of spiritual care consults on patient outcomes, chaplain resident, patient, and chaplain-patient interactions will be tested in mediation analyses using linear regression analysis in order to examine which factors account for improvement in patient outcomes (opioid use, duration of stay, denial of care, patient satisfaction). Any chaplain variables (empathic accuracy or self-reported compassion) that are impacted by CBCT, or patient variables (negative symptoms, well-being) that are impacted by CBCT-informed modules will be entered as independent variables into linear regression analysis with group assignment, and with patient health outcomes as the dependent variable in order to examine whether chaplain, patient, or chaplain-patient interaction variables render group assignment insignificant in accounting for variance in patient health outcomes[^31^](#_ENREF_31).

1. **Compensation:**

No compensation will be provided to participants.

1. **Risks to participation:**

Chaplain residents and Emory Healthcare patients may experience some emotional discomfort while completing the questionnaires. To minimize this risk, all participants will be informed that they are free to skip any questions that are upsetting and that they can stop the questions at any time. In addition, they will be provided help in contacting the Emory Faculty and Staff Assistance Program (FSAP).

In addition, the questionnaires that subjects will fill out as part of this study will contain personal information, and participants may have private pieces of audio recorded.

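### The Aim 5 mediation regressions name no baseline value of the mediator, so for patient mediators the mediator-to-outcome path can be confounded by the pre-consult level.

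*Protocol*

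**What the plan says.** The mediation model stands in the last analysis paragraph of the protocol's Data analysis section. The candidates are introduced as "Any chaplain variables (empathic accuracy or self-reported compassion) that are impacted by CBCT, or patient variables (negative symptoms, well-being"), and those found to be affected by CBCT or by the CBCT-informed modules "will be entered as independent variables into linear regression analysis with group assignment, and with patient health outcomes as the dependent variable". Mediation is then judged by whether the added variables "render group assignment insignificant in accounting for variance in patient health outcomes". The terms named are the mediator(s) and group. No baseline score or other covariate is mentioned, and the paragraph does not say whether the mediator enters as a post-consult score or as a change.

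The Procedures text sets out the patient part of the aim: "We will also examine whether patients’ well-being (hope, quality of life), or negative symptoms (depression, anxiety, loneliness) mediate the impact of spiritual care consults".

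Baselines are collected. Under Design, Sample: "Emory Healthcare patients will be asked to complete self-report assessments before and after their Spiritual Health consult". Under Specific Aim 1, for chaplains: "Empathic accuracy and resilience will be measured for all participants before the early-start group receives CBCT (baseline, or T0"). The only nearby use of a baseline is for the chaplain primary outcomes, which "will be measured as pre-to-post differences in the measurement scores, i.e., T1 – T0". That definition is not carried over to Aim 5 or to the patient scores. For the effect of CBCT-informed consults on patients' symptoms and well-being, the section says "we will conduct independent samples t-tests", with no mention of the pre-consult score.

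**The concern.** A mediation regression has two links: group to mediator, and mediator to outcome. Comparable groups protect the first link only. Nobody assigns a patient a level of depression, anxiety or loneliness, so the second link is an observational association even in a randomised trial. This study is described as naturalistic and describes no randomisation.

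A post-consult symptom score carries much of the pre-consult level. That earlier level may itself be related to duration of stay, opioid use, refusal of care and satisfaction. If it is left out, the mediator's coefficient absorbs that relation, even if the change brought about by the consult does nothing to the outcome. The coefficient of group moves by the same amount in the other direction, and that coefficient is what the protocol's rule inspects.

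At stake is the reading of Aim 5. A patient variable could be named as the route by which CBCT-informed care works when it partly marks who was more distressed beforehand. With change scores, a real route could be masked. The synopsis says the pilot data are to inform a randomised trial.

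**Working it through.** The protocol gives no effect size, correlation, significance level or power for Aim 5, so there is no figure of its own to reproduce. The check asks what the named model returns when the mediator has no effect on the outcome.

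**Inputs from the protocol:** mediator plus group as regressors; 300 patients; self-reports before and after the consult.

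**Assumptions, not in the protocol:** scores in SD units; equal groups of 150; independent patients; CBCT effect on the mediator a = −0.4 SD; pre-post correlation ρ = 0.5 to 0.7; baseline-outcome correlation γ = 0.2 to 0.4; total group effect on the outcome c = −0.33 SD (about 81% power).

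**Set-up.** Let B be the pre-consult score, M the post-consult score, G the group and Y a continuous outcome.

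- M = ρB + aG + error, with unit variance within group
- Y = γB + cG + error, with no M term

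**Post score entered.** Within group, Cov(Y, M) = γρ and Var(M) = 1. The mediator coefficient is γρ and the spurious indirect effect is aγρ.

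- Low end: −0.4 × 0.2 × 0.5 = −0.040
- High end: −0.4 × 0.4 × 0.7 = −0.112
- Share of the assumed total effect: 0.040/0.33 = 12% to 0.112/0.33 = 34%
- Group coefficient left in the model: −0.33 + 0.040 = −0.290 to −0.33 + 0.112 = −0.218

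**Change score entered.** Within group, Cov(Y, M − B) = γ(ρ − 1) and Var(M − B) = 2(1 − ρ). The coefficient is −γ/2 whatever ρ is, and the spurious indirect effect is −aγ/2.

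- Low end: 0.4 × 0.2/2 = +0.04
- High end: 0.4 × 0.4/2 = +0.08
- Group coefficient left in the model: −0.33 − 0.04 = −0.37 to −0.33 − 0.08 = −0.41, so group looks stronger, not weaker

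**Baseline added.** Given B and G, M is unrelated to Y in this set-up, so the mediator coefficient and the indirect effect are zero.

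**Simulation of the protocol's rule** (3,000 runs per setting, post score entered). Group is significant alone and non-significant once the mediator is added in 12% to 33% of runs, against 3% to 4% with the baseline also in the model. These rates do not apply the prior requirement that CBCT be found to affect the mediator.

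**Does that entry requirement protect?** In a separate simulation (2,000 runs per setting, ρ 0.5 to 0.7, γ 0.2 to 0.3, post score, mediator again without effect), both the unadjusted group difference in the mediator and the mediator coefficient were significant as follows:

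| CBCT effect on mediator | Baseline imbalance | As named | Baseline added to both models |
|---|---|---|---|
| 0.3 SD | none | 31% to 68% | 4% to 5% |
| none | 0.3 SD | 10% to 42% | under 1% |
| none | none | 2% to 4% | under 1% |

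The requirement protects when CBCT does not move the mediator and the groups are balanced. It does not protect otherwise, because it tests the other link.

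**The case against.** The strongest objection is that the protocol does not say these are the only terms. It is silent on further covariates and on the form of the score, and an exploratory covariate set may sit in a statistical analysis plan that is not shown. This stands in part: the text does not exclude a baseline. It does, however, write out the regressors and the decision rule, and a reader following it would fit mediator plus group.

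A reader might infer that post-consult scores are planned and that the false-positive rate is therefore known. In the simulation the mediator coefficient is significant in 40% to 99.9% of runs, but the documents do not support that as the plan's error rate. The score form is not stated, the figure ignores the entry requirement, and the protocol judges mediation by the significance of group, not of the mediator. If changes are entered, even the direction differs.

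A reader might also infer that chaplain empathy is affected in the same way. That would need a path from a chaplain's T0 score to a later patient's outcome that bypasses the chaplain's skill at the consult, which is the proposed mediator. The documents give no reason to expect a strong one. A simulation of 30 chaplains with one outcome each does not settle it, because the dependent variable is a patient outcome.

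It is also fair that zero bias after adjustment is built into the check: baseline is the only confounder simulated, it is measured without error, and clustering by chaplain is ignored. Aim 5 is exploratory in a pilot, and Aims 1 to 4 are untouched.

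**Conclusion.** The point holds for patient mediators, in a limited form. As named, the model can confound the mediator-to-outcome path with the pre-consult level, and entering change scores does not cure this. Illustratively, the spurious indirect effect is 0.04 to 0.11 SD in the direction of mediation with post scores, or 0.04 to 0.08 SD in the opposite direction with change scores. Those sizes rest wholly on the assumed correlations and the assumed 0.4 SD effect on the mediator. With post scores the bias vanishes only if the baseline is unrelated to the outcome or to the later score; with change scores, only if it is unrelated to the outcome. It would equally affect a product-of-coefficients estimate, so it is separate from any criticism of the significance rule.

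The documents do not support saying that prior distress will be read as a mechanism, only that it can be. For chaplain mediators the evidence of bias is weak. This is worth correcting, but it does not threaten the primary analysis.

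**What to change.** In the mediation paragraph of the Data analysis section, state the form in which each mediator enters. Add that each patient mediator's pre-consult score, where that instrument is given before the consult, is a covariate in both the mediator model and the outcome model. The qualification matters because the Sample text does not say which instruments are given before the consult, and the spiritual-care outcome measure largely asks about the visit itself.

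For chaplain mediators, add the T0 score as a secondary adjustment. T0 is the common pre-training value for both groups, whereas T2 precedes CBCT only in the delayed-start group. Variables coded from the consult recordings have no baseline and stay as they are.

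The cost is one or two sentences and one covariate per mediator. Each takes a degree of freedom, which is minor with 300 patients and more noticeable for measures taken on at most 30 chaplains. Patients without a pre-consult score would drop out unless a rule for handling them is given. The report should say that the adjustment reduces confounding in this naturalistic study but does not remove it all.

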**Specific Aim 5: To explore chaplain and patient mediators of the impact of spiritual care consults on patient outcomes.**

To examine mechanisms that mediate improved patient outcomes following compassion-informed spiritual consults, chaplains will wear an ambulatory assessment device that records chaplain-patient interactions. Recordings will be coded for (1) use of, and adherence to, the CBCT-informed modules, and (2) compassion language and action. Mediation models will test whether chaplain characteristics, patient characteristics, or chaplain-patient interactions account for improved patient outcomes.

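### Aim 5 judges mediation only by whether the group term loses significance, which is not evidence of an indirect effect and can miss real partial mediation

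*Protocol*

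**What the plan says.** The mediation plan is the last paragraph of the Data analysis section of the protocol. Candidate mediators "will be tested in mediation analyses using linear regression analysis". For chaplain measures, the condition for entry is: "Any chaplain variables (empathic accuracy or self-reported compassion) that are impacted by CBCT". Patient measures (negative symptoms, well-being) have a parallel condition. The selected variables "will be entered as independent variables into linear regression analysis with group assignment, and with patient health outcomes as the dependent variable". This is done "in order to examine whether chaplain, patient, or chaplain-patient interaction variables render group assignment insignificant in accounting for variance in patient health outcomes", with a methodological paper on moderators and mediators (reference 31) cited.

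The paragraph names no indirect effect, no interval, and no condition that the mediator itself predict the outcome.

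Specific Aim 5 adds candidates from the audio recordings: "Recordings will be coded for (1) use of, and adherence to, the CBCT-informed modules".

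The outcomes in the mediation models include opioid use and denial of care. The paragraph just before says: "Dichotomous variables (denial of treatment, opioid use) will be evaluated using chi square tests".

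**The concern.** Mediation means that group changes the mediator and the mediator changes the outcome. Whether the group coefficient crosses a significance threshold after adjustment is a different question, and the answer can mislead in two ways.

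- **Missed mediation.** If part of the effect runs through the mediator and part does not, the remaining direct effect can keep group significant. The rule then points to no mediation although the indirect effect is real.
- **False mediation.** A candidate correlated with group inflates the standard error of the group coefficient even when it has no effect on the outcome. Group can lose significance from collinearity alone.

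The Synopsis says that the active ingredients of chaplaincy care are little studied and that these pilot data will inform a randomized trial. Aim 5 is where mechanisms would be picked out, so a rule that errs both ways could send the next trial after the wrong ones.

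A secondary point is that the model named for opioid use and denial of care does not match the variable type that the protocol gives them.

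**Working it through.** **Inputs.** From the protocol: 300 patients, the criterion, the linear model and the outcome types. Assumed, because the protocol gives none of them: 150 patients per group, two-sided alpha 0.05, independent patients, unit residual SD and the effect sizes. The protocol has no mediation figure to reproduce.

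**Model.** With G = group, M = candidate and Y = outcome:

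- M = a·G + error; Y = c·G + b·M + error.
- Indirect effect = a·b; share mediated = a·b/(a·b + c).
- For a balanced split, the correlation of G with M is r = (a/2)/√(a²/4 + 1), so a = 2r/√(1 − r²).
- Variance inflation VIF = 1/(1 − r²); standard error of the group coefficient given M ≈ √(4/300 × VIF).

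**Step 1, missed mediation.** Take a = 1, b = 0.3, c = 0.4.

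- Share mediated = 0.3/0.7 = 43%.
- r = 0.5/√1.25 = 0.45 and VIF = 1/(1 − 0.20) = 1.25.
- Standard error = √(4/300 × 1.25) = 0.129, and 0.4/0.129 = 3.10.
- Chance that group stays significant ≈ Φ(3.10 − 1.96) = Φ(1.14) = 0.87.

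Simulation (3,000 runs) also gives 87%. In the same data, a joint test of the two paths detects the mediator in over 99% of runs. In other settings with 23% to 33% of the effect mediated, group lost significance in only 1% to 15% of eligible runs.

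**Step 2, false mediation.** Take b = 0 and a group effect of 0.4 SD, and count only runs with a significant total effect (3,000 to 5,000 runs per row).

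| r | Group difference in M (SD) | VIF | Group loses significance | Same, and M has p<0.05 |
|---|---|---|---|---|
| 0.24 | 0.5 | 1.06 | about 3% | below 1% |
| 0.5 | 1.15 | 1.33 | 10% | 1.2% |
| 0.7 | 1.96 | 1.96 | 27% | 2.4% |
| 0.8 | 2.67 | 2.78 | 43% | 2.6% |
| 0.9 | 4.13 | 5.26 | 65% | 2.6% |

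The rate also depends on the power for the total effect. At 80% power it is 6% at r = 0.24, 15% at 0.45 and 39% at 0.71. At 90% power it is 3%, 11% and 32%.

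**Step 3, binary outcomes.** Linear models were fitted to a simulated yes/no outcome with a group term and one mediator. About 8%, 6% and 1% of fitted values fell outside 0 to 1 at assumed baseline risks of 5%, 10% and 40%.

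**The case against.** **The false-mediation rates need large group differences.** This stands. For questionnaire and empathic-accuracy measures a difference of about 0.5 SD is a more natural guess, and there the false rate is about 3%. A reader might take the 43% and 65% rows as what to expect in general. The protocol gives no group-mediator correlation, and those rows need differences of 2.67 and 4.13 SD.

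**An analyst would probably also look at the mediator's own coefficient.** The paragraph speaks of finding which factors account for improvement and cites a methods paper. With that extra condition the false rates fall to 1-3% or less. It is not written down, however, and the contents of the citation cannot be checked here. It also does not cure Step 1 while loss of group significance remains required.

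**The plan says it will examine, not declare, and the mediator coefficient is in the output.** True. In Step 1 the mediator term is significant in nearly every run where group stays significant (86.5% against 86.7% of all runs). The weakness is the criterion, which directs attention away from that coefficient.

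**Coded module use need not be a marker of group.** A reader might infer that it passes the rule automatically or should be barred as a mediator. The documents support neither. Use and adherence may vary among trained chaplains, even r = 0.9 gives 65% rather than 100%, and skill use is a mechanism that Aim 5 asks about. A high correlation with group remains a reasonable worry, since comparison patients are seen by chaplains who have not yet had CBCT.

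**The entry condition cannot be given a power figure.** One might apply a two-sample t-test with 15 residents per arm and report about 26% power for 0.5 SD. The plan states neither that test nor a threshold, and it analyses chaplain outcomes with mixed models, so that figure does not describe the plan. Screening on so few residents (up to 30) is still best avoided.

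**A linear model for a yes/no outcome can be defended as a risk-difference model.** It can, but the protocol does not say so. Its general sentence on departures from normality does not replace the model it names.

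**Conclusion.** The point holds, at minor to moderate severity. The one criterion that the protocol states for mediation is a weak basis for inferring it. The firmer half is missed mediation: about 87% of runs in a scenario with 43% of the effect mediated. The false-mediation half is small for weakly correlated candidates (about 3% at r = 0.24), material at moderate to strong correlation (10% at 0.5, 27% at 0.7), and largely removed if the mediator must also predict the outcome.

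These sizes rest on the assumed split, alpha and effect sizes and on independent patients. They do not model clustering of patients by chaplain, so they illustrate how the rule behaves and do not forecast this study's results. The linear model for two dichotomous outcomes is a real but secondary inconsistency. The primary chaplain outcomes are not touched.

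**What to change.** In the mediation paragraph of Data analysis:

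1. Replace the loss-of-significance criterion with an estimate of the indirect effect and its confidence interval for each named mediator, from a bootstrap that resamples chaplains. Report it whether or not group stays significant.
2. Drop the entry condition as a significance screen, and analyse every named mediator.
3. For opioid use and denial of care, use a model suited to binary outcomes and report a natural indirect effect on the risk-difference scale. Alternatively, state that the linear model is a risk-difference model with robust standard errors. A plain product of logistic coefficients is not advised, because logistic coefficients are non-collapsible and the effects do not decompose simply.
4. If coded CBCT-module use is kept as a mediator, report its correlation with group and interpret it with caution.

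The cost is revised wording and slightly more programming, with no change to data collection. Intervals will be wide and the aim stays exploratory.

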**Patients**

- (<1 min) **NCNN Distress Thermometer**[**^23^**](#_ENREF_23)**:** a single-item distress thermometer that compares favorably with longer measures used to screen for distress.
- (1 min) **PROMIS Self-Efficacy for Managing Emotions**[**^24^**](#_ENREF_24)**:** a likert-27-item scale that measures a subject’s level of confidence to manage and control symptoms of anxiety, depression, helplessness, discouragement, frustration, disappointment, and anger.
- (2 min) **PROMIS Positive Affect**[**^25^**](#_ENREF_25)**:** a 15-item likert-scale that asseses momentary positive or rewarding affective experiences such as feelings and mood associated with pleasure, joy, elation, contentment, pride, affection, happiness, engagement and excitement.
- (4 min) **Hospital Anxiety and Depression Scale (HADS)**[**^26^**](#_ENREF_26)**:** a 14-item questionnaire that is widely used for detecting anxiety and depressive disorders.
- (2 min) **PROMIS Emotional Support**[**^27^**](#_ENREF_27)**:** a 4-item likert-scale that assessed perceived feelings of being cared for and valued as a person.
- (2 min) **PROMIS Informational Support**[**^28^**](#_ENREF_28)**:** a 4-item likert-scale that assesses perceived availability of helpful information or advice.
- (2 min) **PROMIS Social Isolation**[**^29^**](#_ENREF_29)**:** a 4-item likert-scale that assesses perceptions of being avoided, excluded, detached, disconnected from, or unknown by, others.
- (4 min) **Scottish Patient Reported Outcome Measure (PROM)**[**^30^**](#_ENREF_30)**:** an 18-item likert-scale that assesses how a hospitalized patient felt about the Pastoral Care visit both during the consult and after it. It also assesses the patients present state regarding their situation and whether they see themselves as a spiritual or religious person.

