We acknowledge that it could be embarrassing if this information were to become public or fall into the hands of someone not associated with the study. We will take steps to prevent this from happening. All self-report data will be de-identified and stored by a study number, such that these data will be anonymous at all times during data entry and analysis. In addition, all data, including personal identifiers (i.e. name, address, email contact details), will be maintained in secure password-protected electronic files stored on a secure computer system that can only be accessed by study researchers.

1. **Procedures for minimizing risks:**

To minimize the risk that participants become upset while completing questionnaires, the residents will be informed that they are free to skip any questions that are upsetting and that they can stop the questions at any time. In addition, they will be provided help in contacting the Emory Faculty and Staff Assistance Program (FSAP).

Personal identifiers (i.e. name, address, email contact details) will be maintained in secure password-protected electronic files. All of the data collected for these studies will be kept strictly confidential. Under no circumstances will individually identifiable data be released to anyone without the written consent of the subject. Emory Healthcare administrators will not have access to questionnaire data. Results will be discussed with the subjects at their request.

1. **Risk-Benefit Ratio:**

Other people may potentially benefit from what this study reveals. It is hoped that such knowledge will ultimately lead to a better understanding of how CBCT affects the spiritual caregiver in a hospital environment and may inform the application of CBCT to improve patient care. These potential benefits outweigh the minimal risk this research poses to subjects.

1. **Data Safety Monitoring Plan:**

Human subjects’ data to be collected includes responses to questionnaires. Subject data will be identified by ID number, with only the PI and IRB-approved personnel working in her lab having access to the list linking subject names and ID #s. This list will be saved as a password-protected computer file. All data will be collected specifically for the purpose of this research project.

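### The only distress referral in the visible protocol, offered to residents and patients alike, is a programme that by its name is probably meant for employees

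*Protocol*

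**What the plan says.** The section on risks to participation names two groups: "Chaplain residents and Emory Healthcare patients may experience some emotional discomfort while completing the questionnaires". The safeguard that follows covers both: "To minimize this risk, all participants will be informed that they are free to skip any questions that are upsetting", and they may stop at any time. The next sentence is the referral: "In addition, they will be provided help in contacting the Emory Faculty and Staff Assistance Program (FSAP").

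The inclusion criteria in the Design section (Sample) are "Chaplain residents with Spiritual Health at Emory Healthcare or patient of Emory Healthcare", with no exclusions. The same section says that "Emory Healthcare patients will be asked to complete self-report assessments before and after their Spiritual Health consult". The patient measures include a distress thermometer, a PROMIS Social Isolation scale and the HADS, described as "a 14-item questionnaire that is widely used for detecting anxiety and depressive disorders".

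The section on procedures for minimizing risks repeats the safeguard with a narrower subject: "To minimize the risk that participants become upset while completing questionnaires, the residents will be informed" of the freedom to skip or stop. The same FSAP referral follows.

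**The concern.** A referral only helps if the person referred can use the service. The risks section recognises that patients may be upset and then points them to a service whose name suggests that it exists for the institution's employees. A patient upset by the scales who takes up the offer may be sent somewhere that cannot help, and the visible protocol names no alternative.

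What is at stake is the protection of participants, not inference. Nothing here bears on the outcomes, the number of residents or patients, or the analysis.

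**Working it through.** No arithmetic applies. The check is to read the relevant sections against each other.

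1. **Who is at risk.** The opening sentence of the risks section names residents and patients together.

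2. **Who is offered the referral.** The referral sentence says only *they*. The sentence before it has the subject "all participants will be informed that they are free to skip any questions that are upsetting", and the one before that names both groups. The natural reading is that patients are included.

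3. **What is offered.** FSAP is the only service named. Other sections where a patient route might appear do not give one:
   - The section on procedures for minimizing risks names FSAP again, for residents.
   - The Data Safety Monitoring Plan covers storage of data and reporting of adverse events to the IRB and funders. It does not cover support for an upset participant.
   - The section on informing participants of new findings deals with notices about changes in risk and benefit.

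4. **Who the patients are.** Being a patient of Emory Healthcare is sufficient for entry. Some patients may also be employees, but nothing requires it.

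5. **Whether the service fits.** The protocol does not state FSAP's eligibility rules. The name points to faculty and staff. Steps 2 and 4 together mean that the referral covers people who, judged by that name, are probably outside the service.

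6. **How the wording may have arisen.** The section on minimizing risks has almost the same text with residents as its subject. This is consistent with a safeguard written for residents and widened to all participants in the risks section, with the referral left unchanged. That is a plausible explanation, but the protocol does not confirm it.

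**Extent.** One sentence needs correcting and one parallel section needs aligning. The sentence applies to the 300 patients planned under Specific Aim 4. That is the number covered by the offer, not the number who would need it, which the protocol does not give.

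**The case against.** The strongest reply is that the deciding premise is not in the document. No section says that FSAP is closed to patients, so what the text shows is one referral offered to two groups. This stands: the mismatch is probable, not established, and the correction has to allow for the programme accepting patients.

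A reader might go further and infer that distressed patients are left with no support. The documents do not support that. The consent pages are not visible, and a consent form is a usual place for such a contact. The informed consent section requires written consent before any questionnaire is given. Patients complete the scales on hospital campuses, around a spiritual care visit, with study personnel administering the assessments. A usable route very likely exists. These facts lessen the consequence, but none is a written referral, and the visit itself cannot answer distress raised by the scales given after it.

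A reader might also count the patient items that ask about distress and treat the share as a measure of risk. The count depends on what is judged to be about distress, and it says nothing about how many patients would be upset.

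Finally, the residents-only wording in the section on minimizing risks might be read as withdrawing the right to skip or stop from patients. It does not, because the risks section gives that right to everyone. The FSAP sentence in the later section is about residents, so it is not itself misdirected. Only a consistency edit remains there.

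**Conclusion.** The point holds as a minor participant-protection correction. The protocol does more than leave a patient referral unstated: it states one that, judged by the programme's name, probably does not suit most of the people it covers.

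The conclusion rests on three things: that *they* in the referral sentence means all participants; that FSAP's name reflects whom it serves; and that the visible protocol is the only text available to check. If FSAP does take patients, or the consent form names another contact, what remains is a request for the protocol to say so.

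**What to change.** In the section on risks to participation, split the referral. Keep FSAP for chaplain residents. Direct distressed patients to an existing route open to them, such as the treating clinical team, once the sponsor and the IRB have confirmed it. If FSAP does accept patients, say so instead.

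In the section on procedures for minimizing risks, make the safeguard refer to all participants and carry over the same split referral. Check that the patient consent form gives the same contact.

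The cost is wording in two sections and a check with the IRB. If an existing route is named, no new staff, procedure or data collection is needed.
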